## Abstract

**Background:**

Cardiovascular diseases (CVDs) are a leading cause of death and disability worldwide. For people living with CVD, clinical guidelines recommend ongoing self-care such as symptom monitoring, medication adherence, and lifestyle modifications. However, many people struggle to engage in this due to the complexity of disease management, limited understanding, and a lack of cultural support. Conversational agents (CAs) offer a solution by providing artificial intelligence–driven, voice-based support that enables human-like communication. While many CAs and digital interventions are good for people with CVDs, they are for mainstream populations and overlook culturally and linguistically diverse communities.

**Objective:**

This study outlines the protocol for pilot testing the feasibility and usability of Diaspora Engaged Self-Care Intervention and Heart (DESI-Heart) program, to support self-care management among Indian diaspora populations with CVDs in Australia over an 8-week intervention period. The formative development of DESI-Heart is also described.

**Methods:**

We integrated the Double Diamond Model and the ecological validity model to develop our DESI-Heart program. First, we co-designed the program with end users, who identified 4 key goals for engagement with self-care through culturally and linguistically appropriate approaches. Based on these priorities and ideas, we developed specific goals, including (1) medication reminders, (2) daily exercise guidance, (3) diet buddy, and (4) guided meditation. Participants will access the DESI-Heart program through a web-based CA, available on smartphones, laptops, or PCs. Based on their preferred timing, individuals will receive links to access specific components of the program corresponding to each goal. These links will be sent to participants via SMS or email, depending on their preference. A single-arm prepost pilot trial (N=28) will be conducted to evaluate the feasibility and usability of the DESI-Heart program among Indian adults living in Australia with CVDs. The primary outcome will assess feasibility indicators, including recruitment, engagement, and usability, while secondary outcomes will examine changes in self-care behaviors and quality of life.

**Results:**

The DESI-Heart program received ethics approval in July 2024. Recruitment for the pilot trial is scheduled to begin in June 2025 and conclude by September 2025, with participant follow-up expected to be completed by the end of December 2025. All 28 participants have been recruited, and data analysis will be conducted once follow-up is finalized.

**Conclusions:**

We have co-designed and developed the DESI-Heart program, a culturally and linguistically appropriate self-care intervention aimed at supporting Indian adults with CVD living in Australia. The next step is to conduct a pilot study to assess the feasibility and usability of DESI-Heart, which will inform the design of a larger evaluation trial. DESI-Heart has the potential to complement existing health services by helping individuals with CVD manage their condition within the community, while acknowledging their cultural backgrounds and language preferences.

**International Registered Report Identifier (IRRID):**

PRR1-10.2196/78923

## Introduction

Cardiovascular disease (CVD) is the leading cause of death and disability worldwide, contributing to approximately 32% of the worldwide mortality rate [1]. In Australia, CVD contributes 19% to the total disease burden and accounts for approximately 27% of deaths [2]. Clinical guidelines recommend continuous self-care, including symptom monitoring, medication adherence, and lifestyle modification for effective management of these conditions [3]. Self-care is associated with reduced cardiac mortality, hospitalization and readmissions, and increased quality of life [4,5]. However, many individuals often struggle to incorporate and maintain consistent self-care due to complex regimens, limited health literacy, and lack of access to health care support [6,7].

The widespread availability and integration of digital technologies has enabled the development of innovative interventions to support self-care for people living with CVD in the community [8]. A systematic review and meta-analysis (n=9893) found that digital health services, such as mobile health interventions, played a key role in supporting self-care. These interventions were associated with a significant reduction in pain (Hedges g=−1.09; 95% CI −1.68 to −0.45) and disability (Hedges g=−0.77; 95% CI −1.59 to 0.05) [9]. Despite their potential, maintaining long-term engagement with digital interventions is challenging [10] due to users’ lack of health and digital literacy, privacy and security concerns, and the complexity of user interfaces [10-14].

Conversational agents (CA) have emerged as a promising solution to overcome some of these user and engagement barriers by leveraging artificial intelligence (AI)–based systems that use natural language processing, enabling human-like interactions with users [15,16]. CAs offer multiple advantages: (1) the ability to interpret human speech and respond to it in a personalized manner similar to human health care providers [17]; (2) the ability to integrate and connect with technologies (eg, sensors or wearable devices) to provide data driven self-care via a CA [18]; (4) reduce barriers around digital literacy for the user [19]; and (5) capacity to communicate in multiple languages and dialects [20]. However, most CA-delivered self-care interventions have not been developed or adapted to meet the unique needs of culturally and linguistically diverse (CALD) communities [21]. This limits their effectiveness, as cultural factors significantly influence health beliefs and self-management behaviors [22].

Within Australia, the Indian community represents the second-largest immigrant community group, comprising over 721,000 people [23], and this population is at higher risk for poor CVD outcomes, including cardiovascular events, all-cause mortality, and hospitalizations [24]. Additionally, research indicates that more than half of the Indian immigrant population remains closely connected to their cultural values and belief systems, which shape their lifestyle choices and self-care decisions [25,26]. These cultural influences highlight the importance of involving individuals with lived experience of CVDs in the product design process to ensure the development of culturally relevant materials for their use [27].

To address this gap in culturally appropriate CA interventions, we have co-designed a culturally tailored CA intervention (Diaspora Engaged Self-Care Intervention and Heart [DESI-Heart]) to support self-care among individuals with CVD from the Indian diaspora in Australia. DESI-Heart integrates cultural elements specific to Indian communities—including language preferences, traditional health practices, and culturally congruent communication styles. In this protocol paper, we present a comprehensive overview of the co-designed DESI-Heart program, detailing its design and development process guided by established cultural adaptation frameworks. We also outline the planned pilot study to evaluate its feasibility and usability, and potential impact on self-care outcomes.

The primary aim was to evaluate the feasibility and usability of a co-designed culturally tailored CA (DESI-Heart) in supporting self-care management among Indian diaspora populations with CVDs in Australia over an 8-week intervention period.

The primary objectives were (1) to determine participant recruitment rates, retention rates, and adherence to the DESI-Heart program; and (2) to assess the usability of the DESI-Heart program using validated measures of the Bot Usability Scale.

The secondary objective was to evaluate preliminary effects of the DESI-Heart program on changes from baseline to 8 weeks in CVD self-care behaviors and quality of life.

## Methods

### Overview

The reporting and structure of the protocol were guided by the SPIRIT (Standard Protocol Items: Recommendations for Interventional Trials) 2025 statement and checklist [28] (Multimedia Appendix 1).

### Study Design

#### Theoretical Framework

To inform the development of the DESI-Heart program, we used a combination of 2 theoretical frameworks: the Double Diamond Model (DDM) and the ecological validity model (EVM) [29]. The DDM focuses on providing a well-defined and comprehensive representation of design progress in developing novel interventions [30]. The DDM comprises 2 adjacent diamonds, and each diamond represents the process of exploring a problem broadly (divergent thinking) and the process of taking action to resolve the identified problem (convergent thinking) [31]. The DDM model has 4 processes distributed across these 2 adjacent diamonds. The first diamond is termed the problem phase, which consists of two major processes: (1) discover and (2) define. The second diamond is the solution phase, consisting of the other two processes, which are (3) develop and (4) deliver [32]. While the DDM provided the structured design approach, we integrated the EVM specifically to enhance cultural appropriateness and relevance. The EVM model has been used as an effective framework to guide culturally adapted interventions by increasing the ecological and external validity of the intervention [29]. To operationalize this framework, EVM encompasses eight cultural dimensions, which include (1) language used, (2) attributes of persons involved, (3) incorporation of metaphors, (4) identifying content, (5) understanding concepts, (6) achieving culturally adaptive intervention goals, (7) methods involved in intervention, and (8) context of the intervention [29,33]. To address the discover, define, and develop phases, we conducted a co-design study with end users—individuals from the Indian diaspora living with CVDs—using steps 1 to 6 of the EVM process. The deliver phase will involve developing a protocol to test the feasibility, usability, and acceptability of the DESI-Heart program, using steps 7 and 8 of the EVM process (Figure 1).

**Figure 1 figure1:**
[figure not shown]
Logic flow of this study’s framework. CA: conversational agent; CALD: culturally and linguistically diverse; CVD: cardiovascular disease; DESI-Heart: Diaspora Engaged Self-Care Intervention and Heart; EVM: ecological validity model.

#### About CA

The intervention will be delivered using BuddyLink (Great Australian Pty Ltd), a research-grade, AI-enabled CA designed for developing and delivering interventions across various health care contexts [34]. BuddyLink is a validated platform for developing CAs, hosted in secure Australian data centers. The program relies on hard-coded, text- and logic-based conversations, with no AI or large language model principles underpinning its design. However, the current BuddyLink version uses AI in two assistive ways: (1) optional audio transcription or translation with transparent accuracy display, and (2) matching participant free-text inputs to predefined response options. BuddyLink has a proven record of secure, ethics-approved use across government, education, and health care projects, including health research at Deakin University [17,35].

#### Co-Design Results

In DESI-Heart, 4 major goals or modules were identified through co-design workshops with end users: medication reminders, daily exercise activities, diet buddy support, and guided meditations. Each component was specifically developed to address key self-care challenges identified by the Indian diaspora living with CVD (Figure 2).

**Figure 2 figure2:**
[figure not shown]
Screenshots of the DESI-Heart conversational agent. DESI-Heart: Diaspora Engaged Self-Care Intervention and Heart.

The medication reminders will support participants by providing timely alerts to take their medications. Additional features will include the ability to reschedule medication times, snooze reminders, and set alerts for medical appointments and diagnostic tests. Reminders will be scheduled according to the participant’s preferred times. If there are any changes in medication timing or if new medications are added during the program, participants can request updates in their program by informing the research team. The system does not prescribe medications, but only provides reminders, which will also be integrated with the participant’s Google Calendar, allowing them to track their medication schedule alongside other daily activities. However, participants will not have control over modifying this calendar, as it will function as a subscription calendar managed and updated by the research team.

The daily exercise component of the program is designed to support participants in meeting the Australian Physical Activity Guidelines, which recommend at least 150 minutes of moderate to vigorous physical activity per week, spread over 5 days or sessions [36]. To help achieve this, the DESI-Heart exercise program offers short, tailored workout sessions that include clear instructions and demonstrations, prerecorded by trained professionals. Participants will receive tailored exercise videos (≈2 minutes each) based on their preferred time of day. Each exercise will be delivered in 3 sets, scheduled across 5 days per week. Additionally, individuals with specific physical conditions will have access to condition-specific exercises to ensure the content remains safe, relevant, and appropriate for their needs. These exercise sessions are designed to resonate with the Indian community by incorporating culturally relevant content, speech, and delivery style. The demonstrations are led by trained professionals who reflect the participants’ cultural background. This approach was recommended by participants during the co-design workshops, as they expressed a desire for a sense of belongingness with a supportive, familiar presence during their engagement with the program.

Diet buddy is a nutrition education component designed to align with CVD-related dietary recommendations. This feature draws on resources from the recently updated Australian Dietary Guidelines and Australian Guide to Healthy Eating [37]. The content has been culturally adapted to reflect the diverse dietary habits commonly observed among Indian Australian communities. It incorporates both northern and southern Indian food practices alongside typical Australian food practices, ensuring that the program is relevant, inclusive, and accessible to participants from different regional and cultural backgrounds. Delivered gradually over 8 weeks, the program offers culturally tailored content on each food group based on the Australian Guide to Healthy Eating series, including hydration-related guidance and education on healthy sources of protein, fiber, and fats. It also includes convenient and budget-friendly meal and snack plans, meal plating strategies, structured meal plans, a recipe matrix, and practical guidance on incorporating phenolic compounds, polyphenols, and plant sterols to support healthier eating habits. Each week will focus on one of these components over the 8 weeks to ensure thorough education and help inform participants’ dietary practices.

Guided meditation is a key wellness component of the DESI-Heart program. Psychosocial stress is a commonly identified risk factor for CVD, and previous studies have shown that various forms of meditation and yoga can be effective in managing stress and improving CVD outcomes [38]. This component includes several modules, such as guided meditation, mindfulness breathing, and yoga, all of which are prerecorded with clear instructions and guidance from trained professionals. During the intervention period, participants will receive 1 meditation-based (≈10 minutes per meditation) session per day delivered via CA, over 8 weeks. The specific content, duration, and delivery times will be tailored to each participant’s requirements. As with other components of the program, these materials are designed to resonate with the Indian community by incorporating culturally relevant content, language, and delivery styles to foster more engagement and appropriateness of the content.

### Study Overview

An 8-week single-arm prepost pilot trial will be conducted. Participants will receive a personalized DESI-Heart program, which includes the 4 core modules described above, delivered via the CA at their preferred time of day. All assessments will be administered through web-based questionnaires at baseline and at the end of the 8-week program.

### Sample Size

Preliminary calculations using G-power indicated that a total of 28 participants will be sufficient to allow an (estimated) proportion of 80% for recruitment to be estimated with a 95% CI of ±15%.

### Participant and Recruitment

Participants will be adults (18 years and older) living with CVDs, including hypertension, heart failure, atrial fibrillation, coronary heart disease, or peripheral artery disease, and currently residing in Australia. Participants will also have to natively speak any Indian language apart from English; have access to the internet and a smartphone, tablet, or PC.

Participants will be excluded if they (1) have severe symptoms classified as New York Heart Association Class IV, a recent myocardial infarction or unstable angina, were referred to a cardiac transplant unit, or were in palliative care; (2) have severe chronic pulmonary disease; (3) live in a long-term care facility; (4) are unable to participate fully in this study for other reasons, including dementia, life-threatening comorbidities, or psychiatric disorders; and (5) did not identify themselves as part of any Indian community living in Australia. Participants will be recruited via social media (eg, Facebook [Meta]) and through Indian cultural associations, religious organizations, and community networks. To increase accessibility for less digitally literate or socially isolated individuals, we are also promoting this study via faith-based and community organizations, appealing to primary caregivers, and advertising at community gathering places.

### Procedure

After participants have provided informed consent, researchers will schedule a Zoom (Zoom Communications, Inc) or phone call based on participants’ preferences to complete the baseline data assessment. The baseline data assessment will include validated measures of self-care behaviors and quality of life, specifically: Medication Adherence Report Scale-10 [39], Godin Leisure-Time Exercise Questionnaire [40], Cardio-Med Food Frequency Survey Tool [41], and Self-Care Inventory [42]. During this session, participants will provide their sociodemographic details and medication history (Textbox 1).

Feasibility and usability criteria and metrics.
**Green**
If one or more of the green criteria are met, this study will be considered feasible in its current form:At least ≥80% of the target sample size is recruited and enrolled in the Diaspora Engaged Self-Care Intervention and Heart (DESI-Heart) program within 3 months [35]At least ≥80% of participants remain in the DESI-Heart program [43]At least ≥66% of participants completed the set goals delivered via the DESI-Heart program [44]Attrition ≤20% [45]Conversational agent (CA) will be considered usable if the Bot Usability Scale score is >70 [46].

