For each self-care component, the system will deliver culturally tailored instructions and demonstrations followed by questions to determine whether participants completed the activity, their experience, and if they had any concerns. Participants’ responses to these questions will be recorded and saved to the BuddyLink database, enabling the research team to review weekly and modify content as required. During this period, researchers will check in via telephone weekly with participants to address any technical support needs.

After participants complete the 8-week DESI-Heart program, researchers will assist them in completing the follow-up post-study questionnaires online via Zoom. These will include all the questionnaires administered at baseline, minus the demographic questions. Additionally, participants will complete the Bot Usability Scale to report their perceived usability of the DESI-Heart program [46]. During pretesting, we observed that participants will be able to complete the full set of pre- and post-study questionnaires, including instructions, response time, and short breaks, within approximately 50 minutes. This supports the feasibility of administering the selected outcome measures without placing excessive burden on participants. Upon completion of the pilot study, participants will be remunerated for their time and involvement in the study (Figure 3). Subsequently, participants will also participate in an exit interview to better understand their perceptions of the DESI-Heart program, their level of satisfaction, and acceptability.

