### Outcome Measures

The feasibility of this study will be measured using recruitment rates, participant retention, completion of the prescribed self-care program, and attrition. Feasibility will be assessed using criteria outlined in Textbox 1, informed by previous studies [35,43-45] and a “traffic light” system [47], to ensure transparent and standardized progression to a definitive trial. Usability will be assessed by the Bot Usability Scale [46]. Participant scores will be cross-validated with system logs and study records capturing interaction history, which will be accessible through BuddyLink. The usability of the DESI-Heart program is defined as a score of 70 and above, which corresponds to a percentile of 70%, indicating high perceived usability [46].

The secondary outcomes include changes (from baseline to 8 weeks) in participants’ self-care behaviors and quality of life as reported above (Table 1).

**Table 1 table1:** Baseline and follow-up measures.

Assessment or procedure		Screening	Stage 1 (1 week)	Stage 2 (8 weeks)

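### Textbox 1 words the retention criterion as staying in the program for green and amber but staying in the study for red, so the retention row can end with no colour

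*Protocol article*

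**What the plan says.** Outcome Measures in the protocol article lists the feasibility outcomes: "The feasibility of this study will be measured using recruitment rates, participant retention, completion of the prescribed self-care program, and attrition". It refers to the traffic-light criteria of Textbox 1, whose stated purpose is "to ensure transparent and standardized progression to a definitive trial". Retention rates also appear in the first primary objective.

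The retention entries in Textbox 1 are:

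- **Green:** "At least ≥80% of participants remain in the DESI-Heart program". No time point.
- **Amber:** 60% to 79%, again of participants staying in the program. No time point.
- **Red:** under 60%, but of participants staying in the study, and at 8 weeks.

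Attrition is a separate row: green up to 20%, amber 20.1% to 35%, red above 35%. It does not say whether it concerns the program or the study. Goal completion is a further row: green from 66%, amber 50% to 65%, red below 50%.

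The Procedure section describes the week-8 data collection: "After participants complete the 8-week DESI-Heart program, researchers will assist them in completing the follow-up post-study questionnaires online via Zoom". Use of the agent is by prompted links and is tracked by the platform. Researchers also telephone participants weekly.

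**The concern.** The cut-offs 80% and 60% read as one scale, but the event being counted changes between amber and red. Use of the agent and contact with the researchers run through different channels in this design: links on one side, telephone calls and a Zoom session on the other. A participant could therefore stop using the agent and still be present at week 8. On a literal reading that person counts against green and amber but does not count towards red.

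Retention is a primary outcome and feeds a progression decision. If the row can return no colour, or returns amber or red depending on a choice nobody has written down, that choice will be made after the data are seen.

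**Working it through.** **The plan's own figure.** Sample Size gives a half-width of 15 percentage points: "a total of 28 participants will be sufficient to allow an (estimated) proportion of 80% for recruitment to be estimated with a 95% CI of" that size. With the usual precision formula, n = z² p(1 − p) / d² = 1.96² × 0.80 × 0.20 / 0.15² = 27.3, rounded up to 28. At n = 28 the half-width is 1.96 × √(0.16/28) = 0.148. The figure reproduces and is not in dispute. It supplies the denominator of 28, which the Results section says has been recruited.

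**The retention row as written.** Let P be the number still in the program and S the number still in the study at week 8, each out of 28.

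- Green needs P/28 ≥ 80%, so P ≥ 23 (23/28 = 82.1%; 22/28 = 78.6%).
- Amber needs P/28 between 60% and 79%, so P from 17 (60.7%) to 22 (78.6%).
- Red needs S/28 < 60%, so S ≤ 16 (57.1%).

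**Example.** P = 15 gives 15/28 = 53.6%, so neither green nor amber. S = 20 gives 20/28 = 71.4%, so not red. The row has no colour. Counting program use throughout, it would be red; counting study follow-up throughout, amber.

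**When this happens.** The row is empty whenever P ≤ 16 and S ≥ 17. Assuming nobody stays in the program after leaving the study (P ≤ S), there are 29 × 30 / 2 = 435 possible pairs, of which 17 × 12 = 204 have no colour. This counts combinations and is not a probability. None of these cases comes from the gap between 79% and 80%, because no count out of 28 falls there.

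**With one event in all three colours.** Every count has exactly one colour: 0 to 16 red, 17 to 22 amber, 23 to 28 green.

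**Attrition in the same example.** On study follow-up, 8/28 = 28.6%, amber. On program use, 13/28 = 46.4%, red. The attrition row carries the same ambiguity.

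**Attrition as the complement of retention.** If both rows use one event, their cut-offs do not match:

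| Retained | Retention | Colour | Attrition | Colour |
|---|---|---|---|---|
| 17/28 | 60.7% | amber | 39.3% | red |
| 18/28 | 64.3% | amber | 35.7% | red |
| 19/28 | 67.9% | amber | 32.1% | amber |
| 22/28 | 78.6% | amber | 21.4% | amber |
| 23/28 | 82.1% | green | 17.9% | green |

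The clash is confined to 17 and 18 retained.

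**The case against.** The strongest reply is that program and study mean the same thing here. The article defines neither term, the three bands form one continuous scale, and the wording is loose elsewhere: Textbox 1 speaks of enrolment into the program, and the Abstract attaches the ethics approval to the program while Ethical Considerations attaches it to the study. The Procedure section places the final questionnaires after completion of the program and describes no separate follow-up route for people who stopped using the agent. This stands as far as it goes: a single intended event cannot be excluded. But no passage says so, and the three lines would still need one term and one time point.

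A second reply is that this is a condensed article and definitions belong in the full protocol. That would answer a missing definition. It does not answer three printed thresholds that disagree with each other.

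A third reply concerns size. A reader might infer that the trial as a whole could go uncoloured, or that a program most people have abandoned could never be flagged red. The documents do not support either. Wide abandonment would probably push goal completion below 50%, which is red, and the attrition row gives a colour on either reading. Only the retention row is affected.

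A reader might also infer that stopping the program and leaving the study cannot be told apart in the data, or that stopping the agent while staying in follow-up is common. Neither is supported. Engagement logs and week-8 questionnaires are collected separately, and Data Analysis promises observed rates. The Introduction says that long-term engagement is difficult, not that disengaged users still answer.

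**Conclusion.** The point holds as an inconsistency in a printed decision rule for a primary outcome. Read literally, the retention row has no colour whenever at most 16 of 28 remain in the program and at least 17 of 28 remain in the study. This rests on two assumptions: that remaining in the program means still using the agent, which is natural but is an interpretation; and that 28 is the denominator for both rates. If the authors meant one event, what remains is loose wording with the time point stated in only one of three colours, and the remedy is the same.

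The effect is limited to one row of the traffic-light table. The data needed for either reading are collected, and nothing in the article shows how often the two counts would diverge. It is worth correcting because the criteria are meant to standardise the progression decision and the correction is cheap.

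**What to change.** In Textbox 1 and Outcome Measures:

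1. Choose one retention event and use it in green, amber and red, with the 8-week time point and all enrolled participants as denominator.
2. Report the other rate descriptively. If study retention drives the colour, add program use from the BuddyLink logs; if program use drives it, add week-8 questionnaire completion.
3. State which rate attrition complements. If it complements the rate that drives the retention colour, either align the cut-offs or drop the duplicate row, since retention of 60% to 64% is amber while the matching attrition of 36% to 40% is red.

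This needs no new data. All 28 participants are already recruited, so it is a change to progression wording during the study; it should be dated and made before analysis, which the Results section places after the end of follow-up. The price is that the retention figure may look less favourable if program use is the chosen event.
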